**Methods/Design:**

This study is a single-center, prospective, randomized, double-blind explorative trial. Patients with an unruptured intracranial aneurysm admitted to Innsbruck Medical University Hospital for coiling or clipping will be consecutively randomized to either the intervention group (= RIPC by inflating an upper extremity blood-pressure cuff for 3 x 5 min to 200 mmHg) or the control group after induction of anesthesia. Participants will be randomized 1:1 to either the preconditioning group or the sham group using a random allocation sequence and block randomization. The precalculated sample size is *n* = 24 per group. The primary endpoint is the area-under-the-curve concentration of serum biomarkers (S100B, NSE, GFAP, MMP9, MBP, and cellular microparticles) in the first five days after treatment. Secondary endpoints are the number and volume of new ischemic lesions in magnetic resonance imaging and clinical outcome evaluated with the National Institutes of Health Stroke Scale, the modified Rankin Scale, and neuropsychological tests at six and twelve months. All outcome variables will be determined by observers blinded to group allocation. This study was approved by the local institutional Ethics Committee (UN5164), version 3.0 of the study protocol, dated 20 October 2013.

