## Background

Treatment of unruptured intracranial aneurysms involves maneuvers that may lead to cerebral ischemia in up to 60 % of patients [1, 2]. Although the majority of ischemic lesions remain asymptomatic, they may contribute to subtle cognitive deficits after elective aneurysm repair [2]. Ischemia-inducing events during aneurysm repair include brain tissue retraction, deliberate temporary cross-clipping or balloon occlusion of an afferent vessel for proximal control or coil placement, accidental clip occlusion of efferent vessels, thrombosis or thromboembolism during treatment, and other no-flow phenomena of unknown cause.

The effectiveness of interventions for protecting the brain during aneurysm treatment is controversial, and investigation of alternative techniques to increase the ischemic tolerance of the brain, not only during surgery, is desirable [3–5]. Such interventions should be safe, minimally invasive, controllable, cost-efficient, and, when administered during neurosurgical or neuroradiological interventions, practicable in the operating theater and the interventional suite.

*Preconditioning* is one such potential technique to achieve neuroprotection [6]. Preconditioning involves the application of a stimulus near but below the threshold of damage, aiming to protect an end organ from subsequent injury [7, 8]. A variety of stimuli has been shown to induce preconditioning [8]. In *direct* ischemic preconditioning (DIPC), subthreshold ischemia is applied directly to the perfusion territory that may later be exposed to more severe ischemia. In *remote* ischemic preconditioning (RIPC), subthreshold ischemia is induced in an organ or part of the body that is remote from the target organ at risk. The signal is thought to spread systemically by yet unidentified mechanisms [8–12].

Clinical trials using preconditioning prior to interventions that are associated with a high risk of intra-interventional ischemia have been performed in a variety of clinical disciplines [13-28].

Recently, the prevention of secondary damage associated with neural tissue injury itself has come into the focus of preconditioning strategies [29–36]. For example, Dupont-Hoougard and collaborators showed that RIPC, applied during transport to hospital, results in increased tissue survival after 1 month in patients undergoing thrombolysis for acute stroke when baseline levels of hypoperfusion where taken into account [32].

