#### Neuropsychological examination

All patients undergo standardized neuropsychological examination in the week before treatment and at the 6- and 12-month follow-ups in the rooms of the neuropsychological laboratory of the Department of Neurology. Testing will be performed by an experienced neuropsychologist blinded to the preconditioning procedure. The test battery includes the Verbal Learning Memory Test, [79] the Digit Span Test from the Wechsler Memory Scale (WMS), [80] Trial Making Test A/B, [81] Regensburg Word Fluency Test, [82] the Go/No-go Task 2 stimuli 1 target from the Test of Attentional Performance (TAP) [83] and the Hospital Anxiety and Depression Scale (HADS-D) [84].

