#### Statistical analysis

Statistical analysis will be performed by an independent external statistician ([name]). This study is designed as an explorative study to provide data for future confirmatory studies. The main outcome variable (area under the curve, AUC) for each biomarker will be analyzed using intra-operative ischemia as the only explanatory variable in the two groups. No corrections will be made for multiplicity. A difference of ≥ 2 standard deviations (SD) in the main outcome variable is considered to be a statistically relevant effect. The alpha level is set at 0.05 %. The 95 % confidence intervals for the differences will be calculated.

No a priori empirical evidence suggests which of the six chosen biomarkers would be the ideal single primary outcome, but to define the sample size, we allocated the AUC of S100 as the primary outcome. Power analysis aiming to detect a difference of more than two SD in the primary outcome between the groups would require a sample size of *n* = 16σ2/d2 for a two-sided α = 0.05 and 1-β = 0.8 [85]. *N* = 4 patients per group would permit a difference of ≥ 2 SD in serum biomarker levels to be detected in the study population. Assuming that only one in five patients will sustain cerebral ischemia during aneurysm treatment, this would require a sample of *n* = 20 patients per group. Additional 20 % (*n* = 4 patients) per group will be included for unexpected dropouts, unexpected low rates of intra-interventional ischemia or unexpected loss to follow-up. This would require a total study population of *n* = 48 patients (*n* = 24 per group).

All statistical analysis will be performed on an intention-to-treat basis and per protocol. Standard methods of exploratory data analysis will be used for group comparison. Quantitative parameters will be tested for normality and compared using the *t* test or compared with the Mann–Whitney *U* test for non-normally distributed data. Qualitative parameters will be compared using the chi-squared test or Fisher’s test. Group differences for the main outcome variable will be compared using the two-sided *t* test for independent groups or the Mann–Whitney *U* test, as appropriate. Secondary outcome parameters will be compared using the Mann–Whitney *U* test for quantitative data and the chi-squared or Fisher's test for dichotomized outcome data.

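### Cognitive scores are measured before treatment, but the stated Mann–Whitney analysis makes no use of them as a covariate, which costs precision at 6 and 12 months

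*Protocol article*

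**What the plan says.** The section on the neuropsychological examination sets the schedule: "All patients undergo standardized neuropsychological examination in the week before treatment and at the 6- and 12-month follow-ups". The battery covers verbal learning, digit span, trail making, word fluency, a go/no-go task and the HADS-D.

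The abstract lists the corresponding secondary endpoint by its time points only: "neuropsychological tests at six and twelve months".

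The Statistical analysis section names one method for quantitative secondary outcomes: "Secondary outcome parameters will be compared using the Mann–Whitney" U test. The single explanatory variable named there belongs to the biomarker AUC: "intra-operative ischemia as the only explanatory variable in the two groups". For the cognitive scores the article names no baseline covariate, no change score and no repeated-measures model. It gives no SD, correlation or target difference for any cognitive test.

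**The concern.** Cognitive test scores usually differ between patients for reasons that were there before treatment. A two-sample test on follow-up scores leaves those stable differences in the error term, although the design has already paid to measure them. The section on other potential risks puts the added testing at about 2 hours per visit.

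Precision matters here because the effect sought is small by the article's own account. The Background says of silent ischemic lesions that "they may contribute to subtle cognitive deficits after elective aneurysm repair". The trial's product is estimates for later work: "This study is designed as an explorative study to provide data for future confirmatory studies". The Discussion adds that if a primary outcome parameter shows no significant difference, future trials will be planned from the full clinical, imaging and neuropsychological results. An avoidably wide interval for cognition would enter that planning as one of its inputs.

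**Working it through.** **The plan's own figure.** The sample size rests on "16σ2/d2 for a two-sided α = 0.05 and 1-β = 0.8". With d = 2σ, n = 16/4 = 4 per group. Dividing by the assumed one-in-five ischemia rate gives 4 × 5 = 20, and adding 20% gives 24 per group, 48 in total. This reproduces, but it concerns the S100 AUC only. No figure is stated for cognition.

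**Inputs for the check**
- 24 per group, 1:1 allocation (article).
- Two-sided alpha 0.05, from the sample-size sentence. The analysis text prints the level with a percent sign after "The alpha level is set at 0.05"; that conflict is a separate matter.
- Effect 0.5 SD and rho from 0.3 to 0.8: assumptions, since the article gives neither.

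**Formulas** (linear model, equal variances)
- Variance of ANCOVA relative to the unadjusted comparison: 1 − rho².
- Variance of the change score relative to the unadjusted comparison: 2(1 − rho).
- ANCOVA relative to change score: (1 − rho²) / [2(1 − rho)] = (1 + rho)/2. This is below 1 for any rho below 1, so ANCOVA is the more precise of the two.

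**Detectable difference at 80% power, 24 per group** (normal approximation)
- Unadjusted: (1.960 + 0.842) × √(2/24) = 2.802 × 0.289 = 0.81 SD.
- ANCOVA: 0.81 × √(1 − rho²) = 0.70 SD (rho 0.5), 0.58 SD (rho 0.7), 0.49 SD (rho 0.8).

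**Power at 0.5 SD, 24 per group, normal approximation.** Unadjusted: 41%. ANCOVA: 44% (rho 0.3), 52% (rho 0.5), 68% (rho 0.7), 82% (rho 0.8). The gain at rho 0.3 is therefore about 3 points.

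**Power at 0.5 SD, simulated normal data, 24 per group.** Repeat simulations agreed to within about 1 to 2 points.

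| rho | Variance removed (rho²) | Mann–Whitney, follow-up score | Mann–Whitney, change score | ANCOVA |
|---|---|---|---|---|
| 0.5 | 25% | 37–38% | 37% | 48–49% |
| 0.7 | 49% | 37–38% | 55–56% | 64–65% |
| 0.8 | 64% | 37–38% | 73% | 79–80% |

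In simulation, type I error was about 0.05 for both Mann–Whitney and ANCOVA.

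**Where the gain exceeds half.** More than half the variance is removed only if rho² > 0.5, that is rho above about 0.71. The standard error is halved only if √(1 − rho²) < 0.5, that is rho above about 0.87.

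**The case against.** The strongest reply is that the Mann–Whitney test is valid, the endpoint is secondary, the trial is exploratory, and an article without its analysis plan need not say how each score is handled. Much of this stands. What does not stand is that the choice has been left open: the article names the test for quantitative secondary outcomes. An analysis plan that used ANCOVA would depart from the published method.

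Second, the tested parameter may be change from baseline. The article does not exclude this, so a reader who infers that the raw follow-up score is certainly what will be compared goes further than the text. On the change-score reading the loss is smaller at high rho (73% against about 79% power at rho 0.8). At rho 0.5 change scores recover nothing, and below that they do worse than the raw score. ANCOVA is better on both readings.

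Third, a reader might infer that most of the precision is lost. That needs rho above about 0.71, and the article gives no correlation.

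Fourth, a reader might infer that chance baseline imbalance biases the comparison. Such imbalance has an SD of √(2/24) = 0.29 SD units in groups of 24. Randomization means that this is already allowed for in the test's error rate. The cost is imprecision.

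Fifth, adjustment would not make a truly small effect visible. At an assumed 0.2 SD with 24 per group, t-test power is 10% unadjusted, 12% with ANCOVA at rho 0.5 and 16% at rho 0.7. If losses bring the groups to 20, power at 0.5 SD is about 34% unadjusted and 43% adjusted at rho 0.5. This stands, and it limits what the fix can promise.

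Finally, neuropsychology is one of several sources that the Discussion names for future planning. It should not be read as the sole basis of that decision.

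**Conclusion.** The point holds as one of efficiency. A cognitive baseline is collected, and the stated analysis does not use it as a covariate. The unadjusted test is valid and unbiased under randomization, but it leaves rho² of the variance in the error term. At 0.5 SD with 24 per group, moving from Mann–Whitney on the follow-up score to ANCOVA raises power by roughly 10 points at rho 0.5, 27 at rho 0.7 and 41 at rho 0.8 (about 38% to about 48%, 65% and 79%). The gain is negligible near rho 0.3.

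These sizes rest on an assumed effect, an assumed range of rho, normal data and full follow-up. The direction does not depend on whether raw or change scores were meant.

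**What to change.** In the Statistical analysis section, state that each neuropsychological score at 6 and 12 months will be analysed by ANCOVA with group and the pre-treatment score of the same test, or by one repeated-measures model over both visits with the same covariate. Report the adjusted group difference with its 95% confidence interval.

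Fix before unblinding which scores will be transformed or analysed by rank ANCOVA, so that the choice does not depend on the results. Rank ANCOVA does not give a difference in score units, so say how the effect will be reported for those scores. Keep the Mann–Whitney test as a sensitivity analysis.

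The cost is a few sentences of analysis wording and no new data. The one downside is that a simple rule is needed for patients whose baseline score is missing.

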#### Safety of RIPC

With RIPC, the intentional exposure of ischemia-sensitive organs - such as the brain - is avoided by applying stimuli to more ischemia-tolerant tissues like skeletal muscle. Obviously, direct vessel manipulation for introduction of the preconditioning stimulus is also avoided. Although negative effects of IPC cannot be fully excluded, up to now neither experimental nor translational data have documented any negative effects. The IPC protocol that will be employed in our trial has been used in other clinical trials without known adverse events. A phase Ib trial in awake patients investigating the feasibility and safety of IPC using RIPC in the leg did not demonstrate any adverse events associated with RIPC [87]. A discomfort questionnaire was completed by 80 study patients undergoing preclinical RIPC in the arm for suspected cerebral ischemia. None reported any significant discomfort [32].

However, repetitive ischemia in a limb of patients with signs of occlusive peripheral vascular disease may cause additional damage to this limb. Therefore, these patients are excluded from study participation (see exclusion criteria).

Subtle changes in coagulation time (PT and INR, not PTT) were observed in patients undergoing at least four cycles of RIPC after SAH. No hemorrhagic complications were observed in this study [88]. The study was published after enrollment of our first patients. A debate ensued in the steering committee concerning whether patients undergoing stent-assisted coiling (and therefore requiring acetylsalicylic acid and clopidogrel preloading) would be exposed to an increased risk for hemorrhagic complications. One potential study patient was not included for these reasons. After thorough discussion, we concluded from the available evidence that our RIPC scheme (three cycles of upper arm ischemia with the patient under general anesthesia) does not raise safety concerns for the subsequent aneurysm treatment procedure (including stent-assisted coiling).

#### Other potential risks associated with participation in this study

Study inclusion requires anesthesia to be prolonged for approximately 30 min. During this time, the patient is fully monitored and under the supervision of a senior anesthesiologist.

Biomarker determinations will not interfere with the clinical routine in any way. Patients undergoing aneurysm treatment are assumed to undergo preoperative and daily blood sampling for routine monitoring purposes thereafter for at least 5 postoperative days at regular intervals and as deemed necessary thereafter. Participation in the study requires the additional removal of a small amount of blood at predetermined intervals without separate venipuncture. All patients have central venous lines in place according to standard operating procedures. Blood removal is not considered a risk. A separate venipuncture, if necessary in an exceptional situation, can cause discomfort if the patient is awake.

All patients subjected to aneurysm treatment undergo imaging prior to treatment and after the procedure. Study participation requires an MRI in all patients prior to treatment, within 48 h after treatment, at 6 months and at 1 year. Thus, patients who normally would not undergo MRI examination at these time points, that is, in whom ischemia is not suspected on clinical or imaging (CT) grounds, will also undergo MRI. MRI does not involve radiation. Patients not appropriate for MRI investigation will not be included in the study (see exclusion criteria). In artificially ventilated patients, MRI examination will be supervised by an experienced anesthesiologist. The Clinical Departments of Neuroradiology and Anesthesiology of the Medical University of Innsbruck have long-standing experience with MRI examinations in severely ill or intubated neurological patients. Examination of intubated patients is possible 24/7.

Neuropsychological testing will be performed prior to the intervention and at 6 and 12 months during the regular outpatient visits. This additional testing will prolong these visits for approximately 2 hours.

All patients in our departments undergo regular follow-up visits at 4 weeks, 6 months and 1 year after treatment of an intracranial aneurysm. Data concerning functional outcome will therefore be recorded as part of the routine clinical documentation. No additional visits to the outpatient department for study purposes will be necessary. Study participants not willing or able to present for the follow-up visit, for whatever reason, will be contacted by telephone and interviewed using the structured questionnaire published by Bruno [89].

#### Adverse events

Events considered adverse events associated with RIPC therefore include intra-interventional or post-interventional changes in coagulation parameters not commonly seen during neurosurgical or neurointerventional procedures. Severe adverse events include (1) all events that are rarely observed during routine treatment of intracranial aneurysms and that cause a new neurological deficit or require re-intervention, (2) all hemorrhagic complications causing a new neurological deficit, and (3) every ischemic damage to a limb that underwent RIPC.

#### Methods for ensuring quality control and adherence to the study plan

The Department of Neurosurgery has installed a Data Monitoring Committee that meets every week to discuss ongoing studies. All patients who are potential candidates for study inclusion and all RIPAT study participants will be reviewed in this meeting. Additionally, all RIPAT investigators meet at least twice a year to discuss pertinent study progress issues. Prior to study initiation nursing staff was instructed about goals and details of the study. Written SOPs that accompany the various steps of the study (patient screening, preconditioning procedure, taking of blood samples) were issued and made available to all staff.

#### Dissemination

The study protocol following SPIRIT guidelines [90, 91] will be published in a peer-reviewed journal with open access. A report drafted by the principal investigator and authored by all investigators after completion of the study will be submitted for peer-reviewed publication in two parts. The first part, which is due 3 months after the end of patient recruitment, will report on the effects of RIPC on the primary outcome (biomarker concentration) and on short-term neuroimaging changes. A second report concerning clinical outcome will be filed after follow-up of the entire study cohort has been completed. All reports will be linked by citing the registration details. The reports will be prepared according to CONSORT guidelines and its extension to non-pharmaceutical interventions" [92] and comply with the ICH GCP Guidelines for Structure and Content of Clinical Study Reports [93]. The principal investigator will have unrestricted access to the final dataset.

## Discussion

This study uses the elective treatment of intracranial aneurysms as a paradigmatic situation to explore the neuroprotective effects of remote ischemic preconditioning. In this setting, ischemia as visualized by neuroimaging does occur, but is usually not clinically relevant. Nevertheless, serum biomarkers and/or advanced MRI techniques may be able to detect significant group differences between patients who underwent remote ischemic preconditioning and those who did not. In this case, any of these biomarkers may be a candidate as a secondary outcome parameter for future exploration in adequately powered phase III trials aimed at demonstrating a clinically relevant difference as the primary outcome. The primary outcome in such a trial could be the rate of cerebral events assessed within 30 days after randomization. These events comprise death or any new neurological deficit (whether temporary or permanent) attributable to an ischemic lesion detected by neuroimaging. We estimate that, in the setting of a multicenter study involving different institutions and different interventionalists, the rate of such events is 5 % in this patient population and that a reduction of this rate by 50 % would be clinically worthwhile.

In case any primary outcome parameter of the RIPAT trial does not show a statistically significant difference between the treatment and intervention group, the planning of future trials using ischemic preconditioning in this patient group will be based on the analysis of full results including all clinical, imaging, and neuropsychological data.

The study has limitations. First, this is a single-center trial. Second, serum biomarkers in the field of cerebral ischemia may lack the sensitivity and specificity of biomarkers used to monitor cardiac, renal or hepatic ischemia. Third, power analysis for the study is based on the assumption that the determination of a continuous variable, namely the area under the curve of a biomarker, is able to show differences between the treatment and control group. Effects detected by serum biomarkers might be so small that this exploratory study will be found to be underpowered. Fourth, although we use the upper extremity and an established protocol to induce remote ischemic preconditioning, the ideal place and timing for providing protective effects is actually unknown. Fifth, we appreciate that a surgical intervention under total intravenous anesthesia that uses propofol is associated with a large number of stimuli that may also have neuro-altering effects. This may lead to bias. Sixth, two procedures are used to induce focal cerebral ischemia, and although both are believed to be associated with a comparable risk to induce focal cerebral ischemia, the risks may be comparable but not identical.

The strengths of this study are, first, that it explores ischemic preconditioning in a highly standardized clinical situation, namely the elective treatment of an unruptured intracranial aneurysm. In this situation, preconditioning stimulus and ischemic stimulus are time-locked in a highly standardized fashion. Second, we employ a simple, clinically applicable preconditioning technique that was used successfully in other clinical trials investigating end-organ ischemia. If this technique is effective, it may be applicable in many other areas of medicine. Third, the serum biomarkers used to determine the primary outcome are biomarkers that are widely available and that have been used successfully in other clinical trials of cerebral ischemia research.

The results of this trial will not provide a definitive answer to the question of whether remote preconditioning is useful for protecting the brain from ischemia, but are expected to provide data essential to designing larger multicenter phase III trials.

